## Abstract

**Background:**

Hong Kong is experiencing rapid population aging, with the population of older adults expected to reach 36.0% by 2046. The rise in life expectancy is often accompanied by increased chronic diseases and mental health challenges. The healthcare system remains heavily focused on tertiary care, leading to increased system burden and suboptimal health outcomes. Strengthening engagement with primary care for older adults, particularly through community-based services such as District Health Centers, is essential for improving long-term health outcomes. This approach promotes early detection, better management of chronic conditions, and prevention of unnecessary hospitalizations.

**Objective:**

This pilot study aims to evaluate the feasibility, acceptability, and preliminary effectiveness of a hybrid intergenerational home-based and AI-generated digital intervention for increasing the proportion of District Health Center members among older adults in Hong Kong.

**Methods:**

This is a two-group parallel cluster randomized controlled trial, involving 180 older adults recruited from 6 clusters. Participants will receive home-based DHC intervention by trained students, followed by 1-month of AI-generated digital interventions, including infographics, videos, and messages on the introduction and promotion of DHC, via WhatsApp. The feasibility indicators include recruitment rate, retention rates, dose delivered, dose received, and participant engagement. Acceptability outcomes are workshop and digital intervention satisfaction. The primary outcome is to increase the proportion of District Health Center members. Secondary outcomes include the proportion of participants utilizing DHC, health status, behavioral modifiable risk factors, eHealth literacy, infectious disease prevention behaviors, and feasibility metrics. Data will be collected via surveys at baseline and follow-ups (1, 3, and 6 months).

**Discussion:**

This proposed pilot study aims to use hybrid intergenerational home-based and AI-generated digital intervention to improve primary healthcare engagement among older adults in Hong Kong. By promoting awareness and utilization of primary healthcare services like District Health Centers, the study seeks to promote healthier aging, improve health outcomes, alleviate hospital strain, and provide a framework for addressing the needs of aging populations.

**Clinical trial registration:**

https://clinicaltrials.gov/, NCT07252934.

## Introduction

The global aging population is rising rapidly, with one in six people expected to be aged 60 years or older by 2030 (1). In Hong Kong, this situation is one of the most advanced in the world, with the proportion of older adults projected to reach 36.0% by 2046 (2). Over 70% of this large demographic are affected by chronic diseases, and among the most common are hypertension (57.4%) and diabetes mellitus (19.0%) (2–4). These challenges bring increased health service demand, rising medical costs, manpower shortages, and strain on the healthcare system (5). The total health expenditure has grown to 10.0% of GDP in 2022/2023 and is continuing to grow at an annual rate of 5.6% (4, 6). To address these pressing aging challenges and ensure a sustainable healthcare system, a primary healthcare focused approach should be used.

The Hong Kong population has a health-seeking culture that emphasize heavily on acute, episodic medical care, resulting in only 60% of the population maintaining a regular healthcare service (7, 8). This leads to the high reliance on secondary and tertiary care in the healthcare system, with 65.5% of health resources allocated to these sectors (4, 6). To mitigate the overutilization of acute care services, the Government has been working toward a shift from a treatment-focused to a prevention-oriented care (8). Since 2019, District Health Centers (DHCs), have been set up in all 18 districts in Hong Kong. These centers provide primary healthcare services across four categories, including health promotion, health assessment, chronic disease management, and community rehabilitation services (9, 10). The enrolment these primary care centers are vital to initiate the continuity and coordination of care by a professional, interdisciplinary healthcare team (11, 12). It supports systematic long-term health management through advisory health counseling, early detection, and timely treatment (13, 14), which is particularly well-suited to the needs of the older adult population with prevalent chronic conditions (2–4). However, our previous community study of 7,531 older adults showed a low membership rate of 28.9% for DHC, limiting the potential of this resource (15, 16). By increasing awareness, engagement, and utilization of primary healthcare services among this group, it can enhance individual health outcomes, strengthen population health, and contribute to the sustainability and efficiency of the healthcare system (13).

Face-to-face interventions are effective in improving health outcomes among older adults, especially those who are vulnerable and isolated. These interventions allow active reach to home-dwelling older adults who may not engage with healthcare resources, enabling early detection of unmet needs and timely support (17). Home-based interventions directly assess the health and quality of life of participants, as well as the availability of household resources and social support. This context enables more personalized, practical, and effective care planning, ensuring that interventions are tailored to individuals’ real-life needs and circumstances (18).

The initial point of engagement in home visits is followed with digital health communication. There is high smartphone penetration among older adults in Hong Kong, with 90.7% of individuals aged 65 and above owning a smartphone (19). Hence, digital outreach can provide a practical, affordable, and efficient approach to engage the large aging population without the constraints of mobility and time. Digital educational outreach is often used in health communication to induce health behavior changes, it has been used to increase healthcare service uptake (20), improve healthcare appointment attendance (21, 22), promote screening (23), and promote health promotion activities (24, 25). Most of these digital healthcare communications primarily depend on text messaging, and their effectiveness is mixed (20–22). With comparable cost and resources, multimedia integration strategies that combine video, photo, and text can improve user engagement, enhance visual appeal, promote sharing with family and friends, and boost intervention effectiveness (26, 27). In which, a healthcare study on 2,509 patients educating about colorectal cancer screening reported a significant doubling in screening rates when using videos and text compared to text alone (27), demonstrating benefits of multimedia approaches.

Older adults tend to have reduced digital literacy and possess lower education levels. A total of 53.1% of individuals aged 65 or over have a primary education level or below (28). Our previous study also showed an average eHEALS score of 21.41 out of 40, representing low digital literacy among older adults (15, 16). To generate highly tailored multimedia content for overcoming barriers faced by older adults in accessing health information, artificial intelligence will be utilized. Artificial intelligence is beneficial for personalizing health communication content based on target demographics (29, 30), it can also simplify and clarify complex health information for improved understanding (31). The evidence in Generative AI for support of digital behavioral change interventions development is inconsistent (32, 33), though older participants have reported to be more responsive and persuaded by the tailored AI-generated content (29). Whether AI-generated personalized digital intervention content can increase District Health Center membership uptake is unknown.

Both face-to-face and digital interventions are based on the Information-Motivation-Behavioral Skills (IMB) model conceptual framework, a widely recognized, behavior-focused model commonly applied in health education initiatives (34). The IMB framework includes four key elements, which are knowledge, motivation, behavioral skills, and behaviors. It proposes that these components work both independently and together to shape health-related actions. This model was selected because it offers a structured and holistic approach for addressing the multifaceted challenges that older adults face in increasing utilization of primary healthcare (35).

This pilot study will deliver an intergenerational education outreach, with home-based intervention and AI-generated digital health communication, to promote enrolment to local District Health Centers. This will translate into greater success in the adoption and continuity of primary healthcare service utilization behaviors, such as health promotion activities, preventive screenings, and regular check-ups, ultimately overall improved wellbeing. The specific objectives of this study are to: (1) develop a digital intervention message bank personalized for older adults for DHC uptake using artificial intelligence; and (2) evaluate the feasibility, acceptability, and preliminary effectiveness of the education outreach intervention for increasing the proportion of District Health Center members among older adults in Hong Kong.

## Methods

### Study design

The study draws on the data pool collected through the *Generations Connect* (GC) Project, a large-scale community-based initiative aiming to train over 1,000 full-time healthcare students to provide community service and health behavioral coaching to 10,000 older adults in Hong Kong (15, 16). This study is a pilot, two-arm, parallel cluster randomized controlled trial study to evaluate the feasibility, acceptability, and exploratory effectiveness of a hybrid intergenerational home and digital intervention for increasing the proportion of District Health Center membership among older adults in Hong Kong. Data collection will be both offline (face-to-face for baseline) and online (via telephone for 1-month, 3-month, 6-month follow-up) in Nov 2025 - Jul 2026. The study design adheres to the Consolidated Standards of Reporting Trials (CONSORT) reporting guideline (see Figure 1).

**Figure 1 fig1:**
[figure not shown]
CONSORT (consolidated standards of reporting trials) flow diagram of the study.

### Participants

Older adults will be recruited through collaborations with local non-government organizations (NGOs) covering 18 districts across Hong Kong. Older adults are eligible if they (1) are 65 years or older, (2) can speak and read Chinese (including Putonghua and Cantonese), (3) are physically, mentally, and cognitively capable of engaging in simple physical tasks, (4) can understand survey questions, (5) and not a District Health Center member. Recruitment will be conducted in partnership with community centers, senior clubs, and healthcare facilities, which will provide lists of interested individuals.

### Randomization, allocation, and blinding

The recruiting NGO health centers in three geographical areas will be randomized, using a computer-generated sequence, to either the intervention or control arm in a 1:1 ratio. Due to the nature of the study design and intervention, blinding of participants and intervention providers is not feasible. However, the outcome assessors, statistical analysts, and other investigators involved remain blinded to group allocation.

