### Statistical analyses

#### Sample size planning

No formal sample size justification was conducted since this pilot feasibility trial is primarily intended to investigate feasibility parameters and exploratory effectiveness, in order to inform the sample size for a later full-scale trial. Feasibility trials are generally underpowered, and formal calculations are typically not recommended (47). Based on considerations of variability in sociodemographic representation, two NGO partners would be recruited from each of the three geographical regions in Hong Kong, including Hong Kong Island, Kowloon, and the New Territories. A sample size of 30 is expected per cluster. With six clusters, this would result in a total of 180 participants. Given the limited power and cluster, any observed outcomes on intervention effectiveness would be interpreted with caution.

For the qualitative study, a subsample of 18, representing approximately 10% of participants, will be selected. Three people from each cluster will be purposively selected for qualitative data collection. Maximum variation purposive sampling techniques will be used to select participants based on their demographic information, including gender, income, and education level. This sample size would be sufficient to gather a diverse range of experiences and perceptions to identify key thematic patterns.

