#### Data analysis

SPSS Statistics (version 25.0) will be used for data analysis, and an intention-to-treat analysis will be performed. Descriptive statistics will be used to describe demographic variables. For continuous variables, data will be reported as mean ± standard deviation (SD) if normally distributed, or median with interquartile range (IQR) for non-normal distributions. Categorical variables will be presented as frequencies and percentages. To examine exploratory effectiveness given the small numbers of clusters, the binary primary outcome will be evaluated with cluster-level analysis and generalized linear mixed models (48). Missing data will be addressed using multiple imputation with 20 imputations. Statistical significance will be set at a two-tailed *p*-value of 0.05. Statistical analyses will account for the potential effects of intracluster correlation.

For the qualitative interview data, all audio-recorded interviews will first be transcribed verbatim in Cantonese. Two researchers will then independently conduct thematic analysis, with any discrepancies discussed and resolved by a third senior researcher when necessary. NVivo (version 14) will be used for data analysis.

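### Two NGOs are recruited per region, but allocation is not stated to be within region; an unrestricted 3:3 draw would leave two of the three regions unsplit 60% of the time

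*Protocol article*

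**What the plan says.** Under Sample size planning, the Protocol article states that "two NGO partners would be recruited from each of the three geographical regions in Hong Kong", namely Hong Kong Island, Kowloon and the New Territories. The reason given is "Based on considerations of variability in sociodemographic representation". The size follows: "A sample size of 30 is expected per cluster" and "With six clusters, this would result in a total of 180 participants".

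Under Randomization, allocation, and blinding, the unit and method are given: "The recruiting NGO health centers in three geographical areas will be randomized, using a computer-generated sequence, to either the intervention or control arm". The stated allocation ratio is 1:1. The three areas are named in that sentence, but no stratification, pairing or blocking by area is stated.

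Under Data analysis, "the binary primary outcome will be evaluated with cluster-level analysis and generalized linear mixed models". No region term or stratum is mentioned.

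**The concern.** The design uses region when it chooses the clusters, but the text does not say that region is used when the clusters are allocated. With only six clusters this matters more than in a larger trial. Two centres from one region in the same arm are two thirds of that arm, so any regional difference in joining passes largely into the arm difference.

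Region could plausibly matter. The primary outcome is joining a District Health Center, and the home-visit materials (Table 4) treat access as local, with maps, transport, opening hours and booking for the participant's own district centre. The article gives no figures on how joining varies by region, so this is a plausible concern and not a demonstrated one.

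At stake is the precision of the preliminary effect estimate. The pilot is meant to inform a full-scale trial, and an estimate shifted by an unlucky regional draw would carry forward into that planning.

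**Working it through.** **Inputs.** Three regions, two NGOs per region and 30 participants per NGO come from Sample size planning. The 1:1 ratio comes from Randomization, allocation, and blinding, and is read here as three clusters against three.

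**The plan's own figure.** 3 regions × 2 NGOs × 30 = 180 participants in six clusters. This reproduces the stated total.

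**Unrestricted 3:3 allocation.**
- Possible allocations: C(6,3) = 20, equally likely.
- Allocations that split every region: 2 × 2 × 2 = 8 (40%).
- Remaining allocations: 20 - 8 = 12 (60%). In each of these, one region is wholly in intervention, a second is wholly in control, and the third is split. Count: 3 × 2 ordered choices of the two unsplit regions × 2 ways to split the third = 12.
- For any one named region, the chance of being unsplit is 40%. The 60% is the chance that at least one region is unsplit, and whenever that happens there are exactly two.

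**Other readings of the allocation sentence.**
- An independent coin toss per centre: each region splits with probability 1/2, so the chance of at least one unsplit region is 1 - (1/2)³ = 7/8 = 87.5%.
- Allocation within region: 8 allocations, none with an unsplit region, so 0%.

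**Size of the error.** Assume equal cluster sizes, and let a be the effect of the region wholly in intervention, b that of the region wholly in control, and c that of the split region. The region-driven part of the arm difference is (2a + c)/3 - (2b + c)/3 = 2(a - b)/3.

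Take illustrative regional effects of -d, 0 and +d (an assumption):
- 8 of the 20 allocations have |a - b| = d, giving an error of ±0.67d.
- 4 of the 20 have |a - b| = 2d, giving an error of ±1.33d.
- 8 of the 20 have no error.
- The mean error is 0, because every allocation has a mirror image.
- Variance = (4/9) × (8 × 1 + 4 × 4)/20 × d² = 0.533d², so SD = 0.73d.

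| Assumed d (percentage points) | SD of error | Maximum error |
|---|---|---|
| 5 | 3.7 | 6.7 |
| 10 | 7.3 | 13.3 |

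Allocation within region makes this component zero for any set of regional main effects.

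**Adjusting afterwards.** In each of the 12 unbalanced allocations only the split region contains both arms. A region-adjusted effect would then rest on one NGO against one other.

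**Price of restricting.** The smallest two-sided exact randomisation p-value is 2/20 = 0.10 for unrestricted 3:3 allocation and 2/8 = 0.25 for within-region allocation. Neither can reach the stated 0.05 threshold.

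**The case against.** The strongest reply is that the allocation sentence names the three areas and a 1:1 ratio, and the sampling gives exactly two NGOs per area, so one-to-one within each area is a natural reading. On that reading the probability is 0%. The CONSORT diagram is not shown, and a journal article may leave the stratification factors or a region term to the full protocol. This stands: the 60% must be stated as conditional, and the missing region term is not a fault by itself.

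Three stronger readings are tempting, and the documents do not support them.
- A reader might infer that the trial has a 60% chance of regional imbalance outright. The text does not establish an unrestricted draw.
- A reader might infer that region is an established predictor of joining. No regional rates are given. The spread over regions is justified by representation, and the access argument concerns districts, of which there are 18. Two NGOs in one region may therefore face different local centres.
- A reader might infer that the effect estimate would be biased, or that arm and region could not be separated at all. Chance imbalance averages to zero over allocations and forms part of the between-cluster variance that the planned analyses are meant to allow for. One region always stays split, so the effect remains estimable, though very imprecisely once adjusted for region.

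It is also fair to say that this is a pilot, that the article promises caution in reading effectiveness results, and that the feasibility measures can still be estimated after an unbalanced draw. Those points limit the weight of the concern. They do not justify accepting variance that one sentence would remove.

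**Conclusion.** The point holds in conditional form. The design creates three regional pairs, and the stated allocation rule does not commit to using them. If allocation is an unrestricted 3:3 split, there is a 60% chance that one region lies wholly in each arm. The added error in the arm difference then has SD 0.73d and maximum 1.33d, taken over all 20 allocations.

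This rests on reading 1:1 as three clusters per arm, on equal cluster sizes, and on assumed regional effects of -d, 0 and +d, for which the article supplies no values. If regions do not differ in joining, the loss is nil. If allocation is already within region, only the wording needs attention. The issue is avoidable imprecision in the exploratory effect estimate. It is worth correcting because better use of the existing design costs almost nothing.

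**What to change.** In Randomization, allocation, and blinding, state that within each of the three regions one of the two NGOs is allocated at random to intervention and the other to control. This removes the regional main effect from the arm difference. Differences between districts within a region remain.

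For the cluster-level analysis, keep the unmatched comparison of six cluster summaries on 6 - 2 = 4 degrees of freedom. It is conservative after pairing when regions differ, and it avoids the 3 - 1 = 2 degrees of freedom of a paired test. Show the three region-specific differences descriptively.

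The cost is one sentence and no additional clusters. The number of possible allocations falls from 20 to 8, which matters only for an exact randomisation test, and such a test could not reach 0.05 under either scheme. Because the conservative analysis is kept, the true error falls if regions differ, but the reported interval will not reliably become narrower.

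Data collection is scheduled from November 2025, so allocation may already have taken place. If it was done within region, say so. If it was done without restriction, report the number of NGOs per region in each arm beside the primary result.

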### Student interventionists training

Student interventionists are current students enrolled full-time at the University of Hong Kong (HKU) and fluent in Cantonese. Students will be recruited through internal university emails and on-campus promotional materials, such as posters. Recruited students will undergo training provided by research and clinical faculty members before conducting the home-based intervention. A specially designed curriculum will be developed to build knowledge and competence among facilitators on three key domains: (1) knowledge of the research protocol and background, (2) technique in delivering the hybrid intergenerational home and digital intervention on primary health care utilization, and (3) application of the general intervention package (15, 16) (see Table 1).

**Table 1 tab1:** The curriculum content for training student interventionists.

Theme	Training content
Research protocol	The ageing population and the new primary healthcare journey in Hong Kong Effective communication techniques with older adults Home-based intervention protocols and general safety practice guidelines The effectiveness of AI and digital technology in health interventions for older adults
Primary healthcare service utilization	Overview of primary healthcare resources in Hong Kong
General intervention package *Non-communicable disease prevention, mental health and wellbeing, digital health literacy, infectious disease prevention*	Knowledge on non-communicable disease prevention through the promotion of healthy lifestyles Strategies for building positive mental health and wellbeing Assistance with digital devices and mobile-based eHealth services Infectious disease behavioral preventive measures

